## Abstract

**Introduction:**

Anxiety is a common non-motor symptom of Parkinson’s that is associated with reduced life quality, independence and health outcomes. Current anxiolytic medications and the most promising behavioural interventions have inconclusive and mixed results. Occupational therapy is effective at promoting participation in activities of daily living and is recommended in national guidelines. This cluster randomised controlled trial aims to test the feasibility and fidelity of a new occupation-based complex intervention for living well with anxiety in Parkinson’s disease (OBtAIN-PD). No such evidence-based intervention currently exists.

**Methods and analysis:**

50 people with Parkinson’s will be recruited from Devon, UK, to undertake the OBtAIN-PD or usual care delivered by community-based occupational therapists across two National Health Service sites. Recruitment, attrition rates and feasibility of proposed outcome measures (Canadian Occupational Performance Measure, Generalised Anxiety Disorder-7, The Parkinson’s Disease Questionnaire-39, Activity Card Sort, Barthel Index and fall logs) will be tested. Resource data will be collected to aid in the feasibility assessment. Fidelity to content will be assessed using process evaluation. Subjective experiences will be explored qualitatively (10 participants, occupational therapists and decliners).

**Ethics and dissemination:**

This trial has been registered with the ISRCTN registry. Ethical approval has been obtained from the North East - York Research Ethics Committee (reference 23/NE/0027) before data collection. Participants will receive a summary of the results at the end of the data analysis. We will publish the results in a peer-reviewed journal and on institution websites.

**Trial registration number:**

ISRCTN62762494.

STRENGTHS AND LIMITATIONS OF THIS STUDYA diverse patient and public involvement stakeholder group contributed to the design of this study, which increases real-world utility.Outcome measurement is performed remotely, allowing for flexible completion of assessments and increasing efficiency by reducing the burden on participants and staff compared with in-person visits.The cluster design may introduce an imbalance between trial arms, but this should also reduce contamination and improve the study’s internal validity.Assessor blinding might be challenging to achieve in a real-world practice setting, thus introducing the possibility of assessment bias.Follow-up is limited to 24 weeks, which may not capture the long-term effects of the intervention.

## Introduction

### Background and rationale

 Parkinson’s disease, commonly referred to as Parkinson’s, is the second-most common neurodegenerative condition in the UK, affecting approximately 145 000 people.^1^ The cardinal symptoms include tremors, loss of automatic movement and slowed movement.^2^ Parkinson’s also results in sensory, cognitive and psychological impairments that cause significant disability and impede participation in everyday roles and activities, resulting in reduced quality of life.^3 4^ Anxiety affects up to half of people with Parkinson’s (PWPs).^5^ Higher anxiety makes PWPs more prone than age-matched controls to falling and losing independence; it reduces their quality of life, leads to social role dysfunction, reduced participation and increases health burden.^6 7^

The psychological stressors associated with long-term conditions that PWPs experience can increase anxiety.^8^ Furthermore, PWPs may be more susceptible to anxiety than other long-term conditions due to Parkinson’s-associated dopamine deficiency, alongside other factors.^9^ Dopamine is a modulator in the amygdala, a brain structure involved in fear and anxiety.^10^ When dopamine is deficient, this produces neuronal hyperexcitability and exaggerated responses to perceived threats.^9^,^11^ Although PWPs can be treated with dopamine-replacement medication, they often experience a marked increase in symptoms as the medication wears off throughout the day.^12^ Primary (or type-1) worry can, in turn, rapidly progress to type-2 worry (meta-worry or ‘worry about worry’).^13^ This can further increase anxiety symptoms, contributing to the maintenance of the hyperexcited neuronal anxiety circuit.^14^ Thus, as highlighted by the research team’s previous research, living with anxiety in Parkinson’s is a complex experience shaped by neurobiology, individual experiences and life context that restricts participation in meaningful activities.^15 16^

Previous research has highlighted that PWPs living with anxiety place more importance on participation in meaningful roles and activities than group work (the common format for many anxiety treatments).^15^ Restricted participation in everyday activities has a central contributing role to heightened chronic anxiety.^7^ Thus, a participation-focused approach to managing anxiety in PWPs is warranted. Approaches such as cognitive–behavioural therapy (commonly known as CBT) have evidence of effectiveness and acceptability in the Parkinson’s population.^17 18^ Due to the high incidence of cognitive impairment in PWPs, approaches such as CBT often require tailoring to individual PWPs.^18^ PWPs have expressed a preference for interventions focused on meaningful activity and ‘doing’ rather than psychotherapy.^15 19^ In response to these issues, a novel occupation-based complex intervention for living well with anxiety in Parkinson’s disease (OBtAIN-PD) has been co-produced with PWPs, care partners and occupational therapists as part of a logic modelling process using Medical Research Council (MRC) guidance for complex interventions.^20^ During intervention coproduction, participants stated that participation in meaningful activity should be the proposed primary outcome, with anxiety symptoms as a secondary outcome.^15 21^ The OBtAIN-PD intervention can be considered complex because of the number of components involved, the setting, the permitted degree of flexibility and the training needed by the delivering occupational therapists.^20^ This intervention provides a manualised treatment package that targets modifying an individual’s lifestyle, to remove barriers to engaging in activities that are important for PWPs, and is delivered on a one-to-one basis.

As this is a new intervention, no current studies examine the feasibility, acceptability or clinical or cost-effectiveness of the OBtAIN-PD intervention in PWPs.

### Study aims and objectives

Our aim is to conduct a cluster randomised feasibility trial of the OBtAIN-PD in a real-world practice setting. We aim to provide high-quality data to facilitate designing and planning a future definitive trial by answering the feasibility study questions.^22^ Our study objectives are to estimate the feasibility and acceptability of the trial procedures by answering a range of feasibility study questions (figure 1). This trial aligns with the MRC framework for developing complex interventions (figure 2).^20^

**Figure 1 F1:**
[figure not shown]
The OBtAIN-PD feasibility study questions. OBtAIN-PD, occupation-based complex intervention for living well with anxiety in Parkinson’s disease.

**Figure 2 F2:**
[figure not shown]
The OBtAIN-PD feasibility cluster randomised controlled trial in relation to the Medical Research Council framework. Adapted from Skivington *et al*.^20^ OBtAIN-PD, occupation-based complex intervention for living well with anxiety in Parkinson’s disease.

### Study design

This is a pragmatic feasibility cluster randomised controlled trial (RCT), with assessor-blinded outcome assessment, cluster randomising community rehabilitation teams (CRTs) to implement either the OBtAIN-PD and usual occupational therapy care (intervention) or usual occupational therapy care alone (usual care). A cluster randomised design was chosen to help control for potential contamination between trial arms.^23^

Four CRTs across two sites (therefore, two CRTs at each site with one intervention and one usual care) will be allocated on a 1:1 basis to implement the OBtAIN-PD intervention plus usual care, or usual occupational therapy care alone, stratified by site with a block size of two. This will be logistically convenient and accommodate the current pressures on National Health Services while providing a control for contamination. Group allocation will be stratified by site.

## Methods

### Participants, interventions and outcomes

#### Study setting

This trial will be conducted in two National Health Service trusts in the Southwest of England, UK. Each trust will have two CRTs involved in the trial. Each CRT covers a distinct geographical area within their respective Trusts. All CRTs will implement the protocol in the same manner, apart from the treatment they provide, depending on allocation. Occupational therapists within these teams will deliver either usual care alone as part of their routine National Health Service role or the OBtAIN-PD intervention (which includes usual care). The unit of allocation, or cluster, is therefore at the CRT level; two of the four CRTs will be allocated to the intervention group (OBtAIN-PD plus standard care), and two will be allocated to the usual care group (standard care alone). The OBtAIN-PD trial began recruitment in April 2023 and ended recruitment in October 2023. The final 24-week follow-up will be completed in April 2024.

#### Eligibility criteria

All of the following criteria must be met for an individual to be enrolled in the study:

All of the following criteria must be met for an individual to be enrolled in the study:They are over 18 years of age.The person has a diagnosis of idiopathic Parkinson’s, as diagnosed by a neurologist or movement disorder consultant.Experiences anxiety measured as ‘moderate’ (≥10) by the Generalised Anxiety Disorder Assessment (GAD-7) as part of the screening process.Willing and able to undertake eight intervention sessions over 10 weeks.Able to give informed consent.

Individuals who meet any of the following criteria will be excluded:

Participants are unable to give informed consent.People who are unable to physically complete self-report forms and do not have someone to assist them.PWPs experiencing anxiety are measured as ‘mild’ (9 or less) by the GAD-7.PWPs with a severe cognitive deficit that affects their ability to follow instructions are assessed using the Montreal Cognitive Assessment (<23).‘End-of-life stage’ Parkinson’s or other potentially life-limiting condition which is likely to be the main source for anxiety, for example, cancer, heart failure, advanced lung disease.PWPs currently participating in a research study testing an intervention for anxiety or receiving another clinician-delivered non-pharmacological intervention for anxiety that has started in the last 6 months.

#### Interventions

##### Usual care

The usual care group will receive ‘treatment as usual’ occupational therapy care based on that delivered in previous pragmatic trials of occupational therapy for PWPs^24 25^ and guided by both National Institute for Health and Care Excellence guidelines^26^ and the Royal College of Occupational Therapists ‘Occupational Therapy for PWPs’^27^ guidelines. Usual care will be delivered by a community-based occupational therapist at each site (n=2). In the site file, there will be a description of a selection of areas that could be targeted and approaches used. This will include equipment provision, personal care practice and addressing falls. In line with occupational therapy practice, the exact approaches used will be flexible to provide therapist autonomy based on patient needs. The usual care therapy input received by the participants will be recorded to further facilitate a definition of treatment as usual for a future study via intervention logs as part of the case report form. This form will collect the session date, time, duration, location and content. Total participants’ contact time and administration time will be collected to ascertain the impact on the occupational therapists’ time. Treatment as usual duration will last 60 min per session with an estimated eight sessions over a 10-week period based on patient need.

##### Occupation-based complex intervention for living well with anxiety in Parkinson’s disease

OBtAIN-PD is an intervention that focuses on re-establishing and maintaining engagement in meaningful social and habitual roles, like attending a club or engaging in a hobby that PWPs value.^15 16^ In contrast, traditional National Health Service occupational therapy interventions that form the usual care group tend to focus on compensatory techniques (eg, equipment to maintain personal care) that PWPs with anxiety have identified as less of a priority.^15 16^ The OBtAIN-PD has been co-produced with PWPs, care partners and occupational therapists as part of the development phase of the MRC framework for developing and evaluating complex interventions.^20^ The development of OBtAIN-PD is explained in more detail in previous articles.^15 21 28^ The OBtAIN-PD will include lifestyle modification underpinned by acceptance and commitment therapy concepts to help PWPs engage in the meaningful activities that they want to and to live well with their anxiety. The meaningful activities the participants choose to engage with will be individual and may include activities such as walking the dog or attending a social club. Collaborative goal-setting and motivational interviewing concepts will be part of the OBtAIN-PD to promote engagement and adherence. OBtAIN-PD will be delivered by a community-based occupational therapist at each site (N=2).

The intervention will be delivered in community settings, and the occupational therapists delivering OBtAIN-PD will receive specific training in its use. The training consists of a 30 min training video supported by an intervention manual and completed examples of the patient goals and information sheets. Questions will be directed to a research team member (JM) who will act as a gatekeeper to prevent the lead researcher and assessor (CL) from becoming unblinded. The occupational therapists in both trial arms will be based in separate teams and will not share a clinical supervisor to reduce contamination risk. It is estimated that OBtAIN-PD will last 30 min per session, with eight sessions over a 10-week period (n=8).^24 25 29^ The intervention will include an additional 30 min of usual care, that is, 60 min in total. The usual care component will include (but is not limited to) the ordering and provision of aids/adaptations to support participation in care and follow-up contact after delivery to ensure the safe use of the equipment.^30^ The dosage of usual care occupational therapy and OBtAIN-PD are based on published pragmatic trials of occupational therapy for Parkinson’s.^24 25 30^ In summary, OBtAIN-PD will run alongside usual care and provide a novel means of delivering occupational therapy targeting anxiety-related issues in performance. To minimise intertherapist contamination, therapists will be advised to not discuss details of OBtAIN-PD with colleagues.

Participants in both groups will continue to receive usual medical and therapy management, such as physiotherapy. This will be monitored via a health, social care and personal resource-use questionnaire.

### Outcomes

We will conduct both a quantitative and qualitative evaluation. All participants will be requested to complete standardised, validated patient self-reported questionnaires. Electronic, web-based delivery will be used where possible. Paper versions of the questionnaires will be provided with stamped addressed envelopes to return by post for participants who do not have internet access. Email reminders will be used, with telephone calls used when required. The online patient-reported outcome forms will use appropriate completion rules to ensure data completeness.

All measures will be undertaken at baseline and post intervention (12 and 24 weeks following baseline assessment). The follow-up assessments will be anchored to the baseline. This time frame is anticipated to be adequate for delivery intervention, including potential wait times. The 12-week and 24-week follow-ups are important to comprehensively assess potential benefits and the maintenance of any observed effect. All outcome measure activity is summarised in table 1.

**Table 1 T1:** Outcome measure activities

Outcome measured	Instrument used	Screening	Baseline	12 weeks	24 weeks
Self-perceived performance and satisfaction in everyday activities	Canadian Occupational Performance Measure		*✓*	*✓*	*✓*
Participation	Activity Card Sort 3		*✓*	*✓*	*✓*
Anxiety symptoms	Generalised Anxiety Disorder Assessment	*✓*	*✓*	*✓*	*✓*
Health-related quality of life	The Parkinson’s Disease Questionnaire-39		*✓*	*✓*	*✓*
Quality of life	EuroQol 5-Dimension 5-Level		*✓*	*✓*	*✓*
Independence in everyday self-care activities	Barthel Index		*✓*	*✓*	*✓*
Subjective experience	Qualitative interviews				*✓*

### Baseline assessment

Baseline outcome measures will be completed in the week before treatment sessions commence to allow for relevant therapy goal-related information (derived from the Canadian Occupational Performance Measure (COPM)) to be transferred to the treating occupational therapist. If the GAD-7 has been repeated at this point and the participant score is ≤6, indicating a minimal clinically important change^31^ of four points from the inclusion criteria score, the participant will be informed of this and withdrawn from the study. Due to the nature of anxiety in Parkinson’s,^8^ it is anticipated that this will be a rare occurrence. During the initial clinical outcome measure assessment, the lead researcher will complete the Hoehn & Yahr staging. The MDS-UPDRS staging data were initially considered for inclusion, but based on the recommendation of our patient and public involvement (PPI) stakeholders, we decided to omit this additional measure in order to reduce the time burden on participants. The PPI stakeholders believed that this change would help prevent discouraging potential participants. They strongly felt that the trial should focus on exploring the feasibility of using this staging criterion alone while also being aware that additional measures may need to be introduced in future trial designs.

### Proposed primary outcome

The COPM is the proposed primary outcome measure for the future definitive trial undergoing testing. The findings of this study will determine the suitability of the COPM for the future trial. The standard COPM is a valid measure of a person’s self-perception of performance in everyday living^32^,^35^ and has been recommended for PWPs.^36^ The COPM is a client-centred outcome measure for individuals to identify and prioritise everyday issues restricting their participation in everyday living. This measure focuses on occupational performance in all areas of life, including self-care, leisure and productivity and is measured using performance and satisfaction scores. The COPM has been used as a primary outcome in clinical trials of people with neurological conditions including Parkinson’s disease.^24 30 37^ The COPM has a minimum possible score of 1 and a maximum possible score of 10 for performance and satisfaction. An improvement of 0.9 for performance and 1.9 for satisfaction is regarded as clinically significant.^35^ The COPM has adequate content and construct validity, with moderate responsiveness to change in mixed populations of older home-dwelling adults.^38^ This outcome measure will be administered via a secure web-based application or by clinical research teams in person or over the phone if the participant does not have internet access. During the development of this feasibility trial and the OBtAIN-PD, PPI stakeholders felt that participating in meaningful activity was more important than reducing anxiety symptoms alone. Therefore, the COPM was selected as this feasibility RCT’s proposed primary outcome measure.

### Secondary outcomes

The Activity Card Sort (ACS) is an assessment of a person’s perceived level of participation that has demonstrated applications in clinical practice and research.^39^ It will be administered in the same session as the COPM. The ACS is a valid and reliable tool for assessing participation, with excellent intrarater and inter-rater reliability (ICC inter-rater=0.85; ICC intrarater=0.89).^40 41^

The following patient-reported outcome measures will be sent to the participant once informed consent has been gained. These measures will include:

GAD-7: A valid and reliable seven-item instrument used to assess the severity of GAD.^42 43^ The GAD-7 has demonstrated validity and reliability in various populations, with high internal consistency (*α*=0.89).^44^,^46^ The GAD-7 is commonly used in the ‘Improving Access to Psychological Therapies’ pathway. In the future, this will provide a viable way of comparing the OBtAIN-PD against other established UK National Health Service interventions and services that PWPs access. Other Parkinson’s specific scales, such as the Parkinson’s Anxiety Scale, were considered for inclusion in development. On the recommendation of our PPI stakeholders, we omitted this additional measure to reduce the participant’s outcome measure burden and reduce the risk of discouraging potential participants. The PPI stakeholders strongly felt that the trial should explore the feasibility of using the GAD-7 alone. They were made aware that additional measures may need to be introduced in the future trial design. A GAD-7 score of ≥10 identifies a level of anxiety that has a direct impact on the quality of life and is a recommended cut-off that identifies a need for further clinical evaluation.^47^ The GAD-7 is used as both a screening tool and an outcome measure in this trial and will be re-sent to the participant if their first treatment session is not within 1 week of gaining consent.The Parkinson’s Disease Questionnaire-39: This condition-specific questionnaire is a patient-reported measure of health status and quality of life and has been psychometrically evaluated in this population. It comprises 39 questions related to activities and symptoms. It takes approximately 3 minutes to complete. Minimally important changes are available (>25-point change total score, >20-point change symptom subscale).^48^EQ-5D-5L: Evaluation of health-related quality of life. This measure has been used within clinical trials with PWPs and has been psychometrically validated for this population.^49^ The EuroQol 5-Dimension 5-Level version (EQ-5D-5L) can be used to calculate quality-adjusted life-years (QALYs), enabling cost–utility analyses.Barthel Index: A common scale used to measure a person’s performance in self-care activities of daily living and a widely used measure in research to determine the effect of an intervention on independence in these activities.^40 41 50 51^

At monthly intervals throughout the trial, participants will complete a log of falls, resource use and any discomforts they believe to be associated with the OBtAIN-PD study (online or paper-based depending on participant requirements). This log will also collect medication details and any changes to inform analysis, such as introducing anxiolytic medication. The monthly serial collection of data enables the impact of the OBtAIN-PD on these areas to be identified and to assess the suitability of this data collection method, as well as monitor any adverse events (AEs). All patient-reported outcome measures included in this study are validated for use in Parkinson’s disease clinical care and research. The research team designed the falls and resource use log for this study.

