The trial participants cannot be blinded in this trial due to the nature of the intervention they are receiving. Similarly, the National Health Service treating occupational therapists cannot be blinded. The occupational therapists will be aware of their allocation following the randomisation of their CRT. Participants will be aware of the treatment they receive from their first treatment session with the occupational therapist, such as through the receipt of OBtAIN-PD branded materials. The recruiting clinicians (consultants, Parkinson’s nurses, allied health professionals, and CRN research nurses) will not be informed of CRTs’ group allocation. The only exception will be the occupational therapists in the CRTs who will identify potential participants in their usual referral triage process.

The OBtAIN-PD lead researcher conducting all eligibility checks, screening assessments, consent and outcome assessments will be blinded to the participants’ allocated group until database lockdown, along with the team statistician. A second, unblinded statistician generated the group allocation script. Clinical outcomes will be taken remotely wherever possible, and participants will be asked to not reveal their geographic location or the treatment they have received to preserve assessor blinding. At each time point, all outcome measures are patient-reported assessments, thereby minimising the opportunity for the researcher to influence the outcome assessment. Every effort will be made throughout the trial to maintain blinding of the OBtAIN-PD lead researcher, for example, by reminding participants not to discuss their treatment with them.

Assessor blinding will be monitored and tested by recording ‘guess’ participation group allocation at each time point. The blinded OBtAIN-PD researcher will be asked to record on the electronic database any cases of inadvertent unblinding to group allocation at the end of the trial. If this occurs, they will be asked to explain how this unblinding happened. The research team (including the trial statistician) will finally be unblinded after the creation of a locked analysis data set and analysis has been undertaken.

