### Monitoring

The trial monitoring plan has been developed and agreed on by the Trial Management Group (TMG) and Trial Steering Committee (TSC). The TMG will meet monthly. The TSC will meet three times over the 24-month project period, with the first meeting taking place prior to the start of study recruitment. The TSC will include members independent from the trial and an independent chair and statistician.

The likelihood of participants being harmed by the interventions in either trial arm is very low. As such, the collection and reporting of AEs in this trial is restricted only to those events that are classified as serious AEs (SAEs). In the context of clinical care and in accordance with local practice, AEs detected by the treating occupational therapists will be recorded in an electronic case report form. PenCTU will immediately notify a research team member (JM) of any reported AEs/SAEs. This team member will then complete an assessment of the causal relationship.

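### The monthly log takes only discomforts that unblinded participants link to a study named after the experimental treatment, so logged discomforts cannot show the effect of OBtAIN-PD by arm

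*Protocol article*

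**What the plan says.** Under Secondary outcomes, the protocol article describes a monthly log used throughout the trial, in which "participants will complete a log of falls, resource use and any discomforts they believe to be associated with the OBtAIN-PD study". The log also takes medication details and changes. Two of its declared purposes matter here. One is comparative: "The monthly serial collection of data enables the impact of the OBtAIN-PD on these areas to be identified". The other is adverse event monitoring. The same paragraph adds that the trial will assess whether this way of collecting data is suitable, and that the research team designed the falls and resource use log itself.

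Under Allocation, concealment and blinding: "The trial participants cannot be blinded in this trial due to the nature of the intervention they are receiving". Participants learn which treatment they have from the first session, "such as through the receipt of OBtAIN-PD branded materials".

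The name has two uses. In the section on the intervention, "OBtAIN-PD is an intervention that focuses on re-establishing and maintaining engagement in meaningful social and habitual roles". In Study setting, the same name denotes the whole trial.

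Under Monitoring, adverse event collection and reporting is restricted to serious events. Events that treating therapists detect go into an electronic case report form, and one team member assesses causality for reported events.

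**The concern.** A discomfort reaches the database only after the participant has made a causal judgement. That participant knows the treatment received, and the label against which the judgement is made is the brand name of one of the two treatments. Someone who has been given OBtAIN-PD materials has an obvious object to which a new ache or fatigue can be linked. Someone receiving usual occupational therapy has a weaker cue, although that person is in the study too. The same symptom may therefore be logged in one arm and left out in the other.

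The filter acts at the point of entry, so no analysis can restore what was left out. A descriptive table of discomforts by arm could show an excess under OBtAIN-PD that comes from the question and not from the treatment. Because the log is itself under test, a good completion rate could also lead to the item being carried into the definitive trial with this weakness unseen.

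**Working it through.** The plan gives no figure for this item, so there is none to reproduce. The check is a reading of the text followed by an illustration.

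**Text**

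1. Entry condition: the participant's belief that the discomfort is associated with the study (Secondary outcomes). On the natural reading of the sentence, the condition attaches to discomforts only. Falls and resource use stand before it without a condition, and medication changes come in a separate sentence.
2. Who applies it: an unblinded participant (Allocation, concealment and blinding).
3. Label: it names both the trial and the experimental treatment, and only the intervention arm receives a treatment of that name.
4. Use: the log "enables the impact of the OBtAIN-PD on these areas to be identified". In a two-arm trial, impact on discomforts can be read only against usual care.
5. Other channels for a non-serious discomfort: detection by the treating therapist. Therapist contact is estimated at eight sessions over 10 weeks, while follow-up runs to 24 weeks from baseline. Once sessions end, the log is the only channel the article describes for such events.

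**Illustration**

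Let *p* be the true proportion of participants with a discomfort, equal in both arms, and let *q* be the probability that a participant who has one attributes it to the study and logs it.

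- Recorded proportion = *p* × *q*
- Spurious difference = *p* × (*q*_int − *q*_uc)
- Spurious ratio = *q*_int / *q*_uc

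Inputs: about 25 per arm, from the target of 50 split evenly (50 / 2). All values of *p* and *q* are assumptions; the documents give none.

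With *p* = 0.30:

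| *q* intervention | *q* usual care | Recorded, intervention | Recorded, usual care | Difference | Ratio | Expected of 25 |
|---|---|---|---|---|---|---|
| 0.6 | 0.6 | 18% | 18% | 0 | 1.0 | 4.5 v 4.5 |
| 0.6 | 0.4 | 18% | 12% | 6 points | 1.5 | 4.5 v 3.0 |
| 0.6 | 0.2 | 18% | 6% | 12 points | 3.0 | 4.5 v 1.5 |

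Across *p* from 0.20 to 0.50, attribution of 0.6 against 0.2 gives a spurious difference of 8 points (0.20 × 0.4) to 20 points (0.50 × 0.4). Attribution of 0.9 against 0.3 gives 12 points (0.20 × 0.6) to 30 points (0.50 × 0.6).

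The result depends wholly on the attribution gap. With no gap there is no bias, and with a gap in the other direction the sign reverses.

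**The case against.** The strongest reply is that the item says the study, not the treatment. Both arms are in the study. Usual-care participants consented to it, complete its log, and have therapy sessions recorded within it, so they can link a discomfort to it. This stands. A reader might infer that the item asks only about the experimental treatment, or that usual-care participants are bound to report fewer discomforts. The text supports neither. The weakness is an ambiguous label combined with an attribution filter. Under-reporting in usual care is the likelier direction, but it is not certain.

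A reader might also infer that no harms data can be compared between arms. That goes too far. Falls, resource use, medication changes, serious adverse events and therapist-detected events carry no participant attribution condition. Therapists are unblinded as well, but that is a different matter.

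The analysis is descriptive and without hypothesis tests, so the consequence is a misleading description, not a false test result. That also stands. So does the point that the log form is not shown and the article gives one clause about it; the form may already be worded more neutrally. The comment applies to the rule as the article states it.

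Finally, a reader might extend the criticism to the later step, "This team member will then complete an assessment of the causal relationship", because the same team member tells the teams their allocation and takes the intervention therapists' questions. The documents show that this person knows the allocation, but not that the judgement is biased, and relatedness to a treatment is hard to judge without knowing the treatment. I do not press this. That step also means that causality does not depend on the participant deciding it before an entry is made.

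**Conclusion.** The point holds for one item, participant-logged discomforts. As described, entry depends on an unblinded participant's causal belief under a label shared with the experimental treatment. This permits differential capture by arm that cannot be corrected afterwards. The counts cannot carry the comparative use that the article gives them.

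The size is unknown. Under the assumed values above, the spurious difference runs from zero to 30 percentage points, and at a true rate of 30% with attribution of 0.6 against 0.2 it is 12 points. These figures assume equal true rates, about 25 per arm and the attribution probabilities shown. Nothing in the design ensures that attribution is equal, and nothing in the documents shows by how much it differs.

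**What to change.** Ask both arms the same neutral question, without the study or intervention name: any new or worsened discomfort since the last log, whatever its believed cause. Record attribution as a separate item that refers to the therapy received in the study. Report the counts by arm regardless of attribution.

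By the dates in Study setting, recruitment ended in October 2023 and final follow-up falls in April 2024, so logs are already in use under the current wording. Past entries cannot be repaired, and a change during collection would split the series. For entries made under the current wording, label them participant-attributed in the tables and do not read them as a between-arm effect. Do not carry the item unchanged into the definitive trial, even if completion is good.

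The cost is a wording change, one added item and a table label. The downside is somewhat more non-specific entries, such as background Parkinson's symptoms, for participants and data staff to handle.
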